#### Data management

All data get pseudonymized or anonymised by GPs or HPs before they reach the University of Bayreuth and are stored in secure areas. The processing of pseudonymized data from the questionnaires and anonymised transcripts of focus group interviews at the University of Bayreuth is conducted by research assistants who signed a written declaration of confidentiality. Recording of paper documents in separate temporary work files is noted individually, while the objective of double entry with subsequent plausibility checks is to prevent or identify input errors. Once data have been merged into a single, error-corrected working file, this serves as basis for the scientific evaluations. The temporary work files are deleted at this point, the transcripts and paper documents are archived, stored securely and inaccessible to third parties until the end of the evaluation. Only the working file will be stored for 15 years after study ending while all other data will be deleted after the final project report is accepted by the sponsor.

It is explicitly stated that third parties not directly or indirectly involved in the collection or analysis of data are not be granted access to the study data. The data analysis is conducted exclusively by named, contractually employed staff of the VaO project at the University of Bayreuth. All employees are trained in accordance with the data protection guidelines and are contractually obliged to comply with them. No data will be disseminated beyond the results of the evaluations. The results will be provided in an aggregated way with fully anonymised quotations, and do not permit any inferences to be drawn about individual patients.

#### Confidentiality

All data collected for the purposes of the study are confidential and will not be disclosed to third parties. To safeguard any personal data of the participants, all data collected are pseudonymized or anonymised. Pseudonym lists are retained by GPs who provided the information, as are the patient consent forms. As no medical information is required for the study, only the date of birth and sex of the participants are collected. Prior to the commencement of the study, the team received ethical approval from the Ethics Committee of the University of Bayreuth. This approval was granted following the submission of the study protocol including consent forms and questionnaires for assessment.

### Statistical methods

#### Statistical methods for primary and secondary outcomes

Table 1 shows the statistical methods used to analyse quantitative data.

**Table 1 Tab1:** Statistical methods used for quantitative data sets

Data	Points in time	Statistical method
SF- 12	t0, t1, t2	Descriptive statistics, paired t test, ANOVA with repeated measures
ZUF- 8	t0, t1, t2	Descriptive statistics, paired t test, ANOVA with repeated measures
Kilometers	continuous	Descriptive statistics, paired t test, Wilcoxon test
Time	continuous	Descriptive statistics, paired t test, Wilcoxon test

The baseline data (t0) on HRQoL and patient satisfaction are analysed using descriptive statistics. To assess the changes that occurred after the first survey and testing phase, data collected at t0 and t1 are compared using paired t-tests or Wilcoxon test as part of an interim analysis. Upon completion of the second survey and testing phase, all data from the three measurement points (t0, t1 and t2) are subjected to a repeated measures ANOVA to compare outcomes across all three time points.

Additionally, the distance travelled and time spent are compared between the VaO scenario and the home visit scenario. Given the conditions shown, paired t tests or Wilcoxon test are used to determine whether there are any discernible differences in the parameters under examination.

The emphasis is on understanding underlying trends, patterns and on gaining real world evidence.

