## Objectives

The overall aim is to (1) implement the VaO concept in a real-world setting in the Streutal Valley in Northern Bavaria and to (2) evaluate its effectiveness by assessing economic efficiency, satisfaction and HRQoL in compared to the usual care provision.

Therefore, the primary objective is to conduct a health economic evaluation of VaO as a minor modification and resource-saving interdisciplinary form of care to mitigate the shortage of GPs in rural areas. The secondary objective is to test its feasibility and integration into the daily routines of patients, HPs and GPs as well as to evaluate the psychosocial effects of the concept. The following hypotheses are being tested to answer the selected research question.

Hypothesis 1: The monetary expenses and savings of the VaO care model lead to economically neutral to positive results for the GPs running the rooms.Hypothesis 2: The VaO care model reduces average working time spent in nonpatient areas (travel and setup time).Hypothesis 3: The VaO concept does not lead to a change in patients’ HRQoL.Hypothesis 4: The VaO concept does not lead to a change in patients’ and HPs satisfaction.

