### Trial design

The study is designed as a non-randomised, single-arm longitudinal observational study with repeated measurement points in the context of health services research. It is conducted from January 2023 to June 2025, spanning a total duration of 30 months and comprising five phases. The first one, the preparatory phase focused on the requirements of implementation. These were assessed by participating GPs and selected according to the following criteria: (1) village where home visits are carried out (2), number of patients receiving home visits, and (3) share suitable for visiting a VaO room. Suitable premises were selected in collaboration with local mayors. A checklist in accordance with the Association of General Practitioners in Germany (VirchowBund) was used to ensure alignment of the facilities [15]. The criteria included, for example, accessibility, sanitary facilities and stable internet connections. The rooms were inspected by HPs and GPs.

In the initial assessment and testing phase, patients’ care in VaO rooms by their known HPs starts. The HPs continuously monitor the patients’ state of health to determine their suitability for care in VaO rooms [16]. The subsequent interim evaluation and concept adjustment phase aims to correct weaknesses, sources of risk and errors from the initial assessment and testing phase by conducting a focus group interview with the participating HPs on their satisfaction with the use of the room. Sources of risk and errors are targeted while adjustments to the VaO concept optimise processes. In the second survey phase, the time and distance parameters of patient care are continuously collected. A final evaluation is carried out at the end of the study to test the hypotheses.

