### Patient recruitment

Patients are recruited directly by the participating GPs. Patients who meet the following inclusion criteria are contacted directly by their GPs and provided with further information about the study. The final date for patient enrolment is December 31, 2024. Data on travel time, setup time and distance will be collected up to this date. Data on HRQoL and satisfaction will be subjected to analysis for all patients enrolled up to July 31, 2024, in order to be able to map the development over half a year (from t0 to t1).

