##### Costs

The costs of the innovative form of care are calculated using the existing remuneration models for medical assistants in job group IV of the German Collective Labour Agreement for Medical Assistants. The average salary and the average monthly working time of a full-time HP are calculated using the collective agreement for medical assistants of the Bavarian Medical Association [21, 22]. The exact values are one basis for calculating the expected cost savings from VaO.

To measure the cost-effectiveness of the intervention, the incremental cost-effectiveness ratio (ICER) of the innovative care system VaO in comparison to the standard method of care is calculated. Mathematically, the ICER sets the difference in costs in relation to the difference in benefits and allows to illustrate the drivers and limitations (e.g., effects of VaO room utilisation, logistical challenges) of cost-effectiveness:

$$\mathrm{ICER}\;=\;({\mathrm C}_{\mathrm{VaO}}-{\mathrm C}_{\mathrm{standard}})/({\mathrm B}_{\mathrm{VaO}}-{\mathrm B}_{\mathrm{standard}})$$

C_VaO_ includes the calculated costs of the care system VaO, namely, room rent (including maintenance and cleaning), which is calculated from the local standard comparative rent, as well as the costs of travel distances and times according to the VaO route planning when using the VaO rooms.

C_standard_ includes the cost of travel distances and times according to standard route planning.

B_VaO_ includes the benefit expressing change in satisfaction and HRQoL from t0 to t1 and t2 as mentioned above as a reflection of the satisfaction with the innovative form of care.

B_standard_ includes the benefit expressing average HP and patient satisfaction at time t0, reflecting satisfaction with their usual form of care.

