## Discussion

VaO addresses several healthcare challenges through its straightforward design and use of existing resources. The study aimes to explore the effective use of scarce human resources, to maintain the relationship between GPs, HPs and patients, and to extend the concept of delegation. The implementation of the care plan achieves its objectives with minimal changes to the location of service provision while generating real-world evidence within the context of everyday care.

Due to the geographical limitations of the project region and the strict health policy criteria regarding home visits, the study is expected to have a relatively small number of participants. A control group was omitted since the development of HRQoL and patient satisfaction across the three observation points uses a repeated measures design. While the first measurement t0 is placed at the baseline before starting the intervention, t1 and t2 show the development after six resp. twelve months of testing and data collecting.

This design is considered appropriate for evaluating the form of care. Repeated measurements enable the assessment of long-term effects [23, 24]. Moreover, comparing the two scenarios before and after implementation allows for the identification and discussion of any observed improvements or deteriorations. However, it is not possible to directly attribute the observed changes in HRQoL to the implementation of the new care concept due to uncertainties about causalities [25].

A study by Mergenthal et al. revealed that 59% of GPs surveyed had their home visits carried out exclusively by HPs. The study also revealed that HPs are often employed in rural areas allowing the GPs to save a significant amount of time [26]. In combination with VaO and the expected savings in working time in the nonpatient area, GPs could be relieved to a greater extent. The authors see the most significant advantage of the project in this enhanced efficiency. Given that the spatial alterations are minimal, the actual care remains unaltered, and there is no expected loss of quality.

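### The ICER counts the uncontrolled change in HRQoL and satisfaction as VaO's benefit, and Hypotheses 3 and 4 are worded as VaO effects, although the protocol says HRQoL change cannot be attributed to VaO

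*Protocol article*

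**What the plan says.** **Design.** Under Trial design: "The study is designed as a non-randomised, single-arm longitudinal observational study with repeated measurement points". The Discussion gives the reason for having no comparator: "A control group was omitted since the development of HRQoL and patient satisfaction across the three observation points uses a repeated measures design".

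**Hypotheses.** Under Objectives, Hypothesis 3 (HRQoL) and Hypothesis 4 (satisfaction of patients and HPs) share one form: "The VaO concept does not lead to a change in patients" and so on. Trial design adds that the final evaluation is to test the hypotheses.

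**Analysis.** Under Statistical methods for primary and secondary outcomes, "data collected at t0 and t1 are compared using paired t-tests or Wilcoxon test as part of an interim analysis". All three time points then go into a repeated-measures ANOVA, which the Sample size section sets up with a single group.

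**ICER.** Under Costs, the VaO benefit term "includes the benefit expressing change in satisfaction and HRQoL from t0 to t1 and t2". The standard-care benefit term is average HP and patient satisfaction at t0.

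**Stated limitation.** The Discussion says "it is not possible to directly attribute the observed changes in HRQoL to the implementation of the new care concept". The Abstract says the same. Neither extends the statement to satisfaction.

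**The concern.** With one group, time since t0 and time under VaO care are the same variable. Whatever would have happened to these patients under continued home visits, such as ageing or progression of chronic disease, is part of every t0-to-t1 and t0-to-t2 change. Repeated measurement removes stable differences between patients. It does not remove change over time, so it cannot replace a comparator as the Discussion suggests.

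That would be an accepted limit if the protocol only described change. It goes further in two places. Hypotheses 3 and 4 make the result a statement about what VaO causes, and the ICER divides a cost difference by a benefit built from the uncontrolled change. The health economic evaluation is the primary objective, so a reader could take from it a cost per unit of benefit that the authors themselves say they cannot assign to VaO.

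The error can run either way. Background decline would count against VaO. Background change opposite to a real VaO effect would support a finding of no change.

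**Working it through.** **1. Reproduce the plan's figure.** Inputs from Sample size: effect size f = 0.25, alpha 0.05, one group, m = 3 time points, correlation 0.5, nonsphericity correction 1. For the within-patient F test:

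- lambda = f² × N × m / (1 − rho) = 0.0625 × 28 × 3 / 0.5 = 10.5
- df = 2 and (28 − 1) × 2 = 54
- power = 0.812 at N = 28, and 0.796 at N = 27

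The stated N = 28 and power 0.81 are correct. The sample size arithmetic is not at fault.

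**2. What the test sees if VaO does nothing.** The documents give no background change, so I assume a linear drift of D standard deviations over 12 months, with means 0, D/2 and D. Then f = D × √(1/6), and lambda = (D²/6) × 28 × 3 / 0.5 = 28 D².

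For the t0-t1 paired t test the shift is D/2. The SD of the difference is √(2 × (1 − 0.5)) = 1, so the noncentrality is (D/2) × √28.

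| Assumed drift over 12 months | ANOVA lambda | ANOVA rejects no change | t0-t1 noncentrality | Paired t0-t1 rejects |
|---|---|---|---|---|
| 0.1 SD | 0.28 | 7.0% | 0.26 | 5.7% |
| 0.2 SD | 1.12 | 13.8% | 0.53 | 8.0% |
| 0.3 SD | 2.52 | 26.2% | 0.79 | 11.9% |
| 0.4 SD | 4.48 | 43.7% | 1.06 | 17.5% |

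Without drift both tests reject in 5%. Setting D × √(1/6) = 0.25 gives D = 0.61, so a pure drift of 0.61 SD would be flagged with the same 81% power as a VaO effect of the planned size.

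**3. Masking.** Take a real linear VaO effect of 0.612 SD (the planned f) and an assumed opposite drift of 0.3 SD. The net shift is 0.612 − 0.3 = 0.312 SD and lambda = 28 × 0.312² = 2.73. The chance of detecting any change falls from 81% to about 28%.

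**4. Set the statements side by side.**

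| Place | HRQoL | Satisfaction |
|---|---|---|
| Objectives, Hypotheses 3 and 4 | worded as an effect of VaO | worded as an effect of VaO |
| Costs, VaO benefit | t0-to-t1/t2 change counted | t0-to-t1/t2 change counted |
| Statistical methods | no term separating time from VaO | no term separating time from VaO |
| Abstract and Discussion | change not attributable to VaO | silent |

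The HRQoL column contradicts itself. The satisfaction column has the same confounding with no reservation.

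**The case against.** **The limitation is disclosed.** It appears in both the Abstract and the Discussion, and the study is framed as an observational proof of concept. This stands: nothing is hidden, and a single arm is not in itself the defect. But the disclosure changes neither the hypotheses nor the ICER.

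**The statistical methods attribute nothing.** A reader might infer from the t0-t1 sentence that the tests themselves credit the change to VaO. They do not. That section speaks of assessing changes that occurred and of understanding trends. Attribution enters only through the Objectives and Costs sections.

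**Season.** A reader might infer a seasonal bias, since t0 and t1 lie six months apart: "in order to be able to map the development over half a year (from t0 to t1". The documents do not support building on this. They do not say how enrolment was spread. Under uniform entry from 22 May 2023 to 31 July 2024, only about 0.15 of an assumed sinusoidal summer-winter swing carries into t0-t1, and about none into t0-t2. The t0-t1 test is an interim analysis. Winter travel to a room is also part of what VaO changes, so adjusting for season could remove a real effect. Leading with t0-t2 instead has its own cost: patients enrolled in July 2024 reach 12 months in July 2025, after the study ends in June 2025.

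**The ICER denominator is not a clean change.** As written, the VaO term is a change and the standard-care term a t0 satisfaction level. This is true, and a separate defect. It does not rescue the VaO term, which still contains all uncontrolled change.

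**Reach.** HRQoL and satisfaction are secondary outcomes. The time and distance comparison is between modelled routes and is unaffected. Hypothesis 1 concerns monetary expenses and savings only. This also stands.

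**Conclusion.** The point holds for the ICER and for the wording of Hypothesis 3 and the patient part of Hypothesis 4. For HRQoL the protocol contradicts itself. For satisfaction it omits a caveat that applies equally.

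The size depends on a drift that the documents do not give. Over an assumed linear range of 0.1 to 0.4 SD in 12 months, with no VaO effect, N = 28, correlation 0.5 and sphericity, false rejection of no change is about 7% to 44% (ANOVA) and 6% to 17.5% (paired t0-t1). A reader might infer that ordinary decline would lead to rejection of Hypothesis 3. The figures do not support that: non-rejection remains the likelier result throughout this range. The contradiction itself rests on the text alone and needs no drift assumption.

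**What to change.** 1. **Objectives.** Restate Hypothesis 3 and the patient part of Hypothesis 4 as: HRQoL (patient satisfaction) does not change during 12 months of VaO care.
2. **Abstract and Discussion.** Extend the non-attribution statement to satisfaction.
3. **Costs.** Do not use the uncontrolled change in HRQoL or satisfaction as VaO's incremental benefit. Report it descriptively beside the cost difference, in cost-consequence form.

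The tests under Statistical methods can stay as they are, read as tests of change over time. No new patients or data are needed. The price is a narrower claim, and no cost-effectiveness ratio based on HRQoL or satisfaction.

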### Dissemination plans

The results of the study will be published in open access peer-reviewed journals. To maximise the impact of the project and to support the dissemination of its results including knowledge transfer with the scientific community, the scientific results will be published in high-ranked journals and presented at considerable congresses. Furthermore, relevant stakeholders including researchers, practice owners, healthcare professionals and policy makers, will be informed directly through appropriate channels.

## Discussion

VaO addresses several healthcare challenges through its straightforward design and use of existing resources. The study aimes to explore the effective use of scarce human resources, to maintain the relationship between GPs, HPs and patients, and to extend the concept of delegation. The implementation of the care plan achieves its objectives with minimal changes to the location of service provision while generating real-world evidence within the context of everyday care.

Due to the geographical limitations of the project region and the strict health policy criteria regarding home visits, the study is expected to have a relatively small number of participants. A control group was omitted since the development of HRQoL and patient satisfaction across the three observation points uses a repeated measures design. While the first measurement t0 is placed at the baseline before starting the intervention, t1 and t2 show the development after six resp. twelve months of testing and data collecting.

This design is considered appropriate for evaluating the form of care. Repeated measurements enable the assessment of long-term effects [23, 24]. Moreover, comparing the two scenarios before and after implementation allows for the identification and discussion of any observed improvements or deteriorations. However, it is not possible to directly attribute the observed changes in HRQoL to the implementation of the new care concept due to uncertainties about causalities [25].

A study by Mergenthal et al. revealed that 59% of GPs surveyed had their home visits carried out exclusively by HPs. The study also revealed that HPs are often employed in rural areas allowing the GPs to save a significant amount of time [26]. In combination with VaO and the expected savings in working time in the nonpatient area, GPs could be relieved to a greater extent. The authors see the most significant advantage of the project in this enhanced efficiency. Given that the spatial alterations are minimal, the actual care remains unaltered, and there is no expected loss of quality.

### Trial status

Version 1, status 31/03/2023. Recruitment began at 22/05/2023 and is still ongoing until 31/12/2024. Trial was registered at the German Clinical Trials Register (DRKS00033915) – Registration Date 19/03/2024.

## Data Availability

No datasets were generated or analysed during the current study.

## Abbreviations

AGnES: Physician-relieving, community-based, e-health-supported, systemic intervention (Arztentlastende, Gemeindenahe, E-Health-gestützte, Systemische Intervention)
DMC: Data monitoring committee
GP: General practitioner
HP: Healthcare professional
HRQoL: Health-related quality of life
ICER: Incremental cost effectiveness ratio
KVB: Bavarian Association of Health Insurance Doctors (Kassenärztliche Vereinigung Bayern)
NäPa: Nonphysician practice assistants (Nichtärztliche Praxisassistenz)
OECD: Organisation for Economic Co-operation and Development
SF-12: Short-Form 12
VaO: VERSORGT am ORT (engl. “PROVIDED on SITE”)
VERAH: Care assistants in the GP practice (Versorgungsassistenz in der Hausarztpraxis)
